## Outcome measures

### Primary outcome measures

#### Caregiver Burden Scale

The Caregiver Burden Scale is a measurement tool developed by Vadivelan K et al., through empirical analysis involving caregivers of children with disabilities in Tamil Nadu, considering sociocultural factors. It comprises 15 items rated on a 5-point Likert scale, ranging from 'strongly disagree' (1) to ' strongly agree' (5) [5]. This scale has demonstrated strong internal consistency, with a Cronbach's alpha exceeding 0.8. [17]. The higher the burden, lesser the quality of life.

## Outcome measures for preliminary screening

### Little Developmental Coordination Disorder Questionnaire (Little DCDQ)

Little Developmental Coordination Disorder Questionnaire (Little DCDQ) is a parental assessment tool designed to screen children aged 3 to 5 for developmental coordination disorder. It exhibits good validity (0.73–0.87) and shows high agreement with the Movement Assessment Battery for Children – 2 (MABC-2). Little DCDQ comprises 3 domains, each containing 5 items, assessing fine motor skills, execution control, and overall coordination. Responses are rated on a 5-point Likert scale, with specified cutoff values for DCD classification and screening. [18].

## Ages and Stages – 3 (ASQ—3)

ASQ 3 developed by Squires and D. Bricker, is a parent-administered screening tool with five domains covering gross motor skills, fine motor skills, communication, personal-social interactions, and problem-solving abilities. ASQ—3 is strongly endorsed by the American Academy of Pediatrics due to its robust psychometric properties and user-friendliness. It demonstrates high sensitivity and specificity in identifying developmental delays in children aged 2 to 60 months and shows good agreement with DASII and Bayley scales.[19, 20].

## ADHD rating scale IV – preschool version

The ADHD Rating Scale IV – Preschool Version is a reliable tool for detecting ADHD in children aged 3 to 5 years. Parent rated version had established an excellent test–retest reliability (0.85–0.95) and an internal consistency of 0.95. Scale consists of 18 items rated on 4-point likert scale (0-never/rarely to 3 – very often) [21].

## Indian Scale for Assessment of Autism (ISAA)

ISAA was created by the National Institute for the Mentally Handicapped to diagnose and assess the severity of autism. The scale has 40 items under 6 domains scored based on 5-point likert scale. The interpretation of scores are: no autism (score < 70), mild autism (scores between 70–160), 107–153 (Moderate autism) and severe autism (> 153). [22]. It demonstrates reasonable sensitivity in screening for autism in children aged 2–5 years. [23].

## Statistical analysis

The collected data will be entered into a database and analyzed using SPSS. Baseline demographics including participant details, obstetric history, educational status, family history and other relevant details will be visualized using Tableau. Baseline characteristics will be summarized as frequencies and percentages for categorical variables and as means ± standard deviations (or medians with interquartile ranges for non-normally distributed data) for continuous variables. Inferential statistics: Chi-square test: We will use this to analyze associations between categorical variables, such as caregiver burden severity and prior diagnosis of neurodevelopmental disorders (NDD). t-test: Applied to compare means between two groups, such as pre- and post-intervention caregiver burden scores.

ANOVA: Used to compare differences in continuous outcomes, such as caregiver burden scores and child developmental outcomes, across multiple groups (e.g., different clinics or geographic regions).

Regression analysis: Binary Logistic Regression: This will help us identify the impact of the intervention on the binary outcome (reduction in caregiver burden, yes/no), controlling for potential confounding variables (e.g., socioeconomic status, severity of NDD).

Visualization tools: Tableau will be used to create dashboards summarizing key indicators, such as clinic utilization, caregiver burden trends, and regional prevalence rates.

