## Procedures

Given the need for a comprehensive understanding of the local community to plan a specialist outreach clinic effectively, this study will be conducted in phases to assess prevalence, healthcare needs, and resource availability. This is crucial for establishing a specialized outreach clinic in a village. [16].

The initial phase of the research will entail the gathering of fundamental data from the twelve villages adopted by SRMIST namely, Kolathur, Chettipuniyam, Orathur, Nattarsanpattu, Anjur, Thenmelpakkam, Pattaravakkam, Kalivanthapattu, Baburayanpettai, Minnal Chithamur, Kilathivakkam and Chunambedu.

The fundamental details will include information on the number of panchayats (basic governing institution in Indian Villages), anganwadis(Rural child care centre in India), and the demographics of preschool children registered in Anganwadi.

Subsequent to the fundamental data collection and establishment of a rapport with the Panchayat authorities and Anganwadi personnel, a preliminary screening will be conducted by physiotherapists on all Anganwadi children aged between 3 to 5 years in 12 SRM UBA adopted villages after obtaining the parental consent. This screening aims to comprehensively enumerate data for determining the prevalence of Neurodevelopmental Disorders (NDD) among these children. The rapport established with village authorities will help in gaining confidence of common people and will help in improving their adherence.

Physiotherapists, in collaboration with parents, will complete a screening checklist. This checklist will primarily focus on detecting developmental delays, DCD, autism, and ADHD, as these are the most commonly observed NDDs among preschoolers. Information on children previously diagnosed with NDD and their history of treatment/rehabilitation will be gathered retrospectively.

Upon identifying the prevalence of neurodevelopmental disabilities, model centers will be established in villages with high prevalence rates. Consideration will be given to ensuring that these centers are accessible to the entire population, including nearby villages by discussing with the village heads. The establishment of model clinics will be based on the identified needs. While the initial plan is to set up one model center, if the prevalence is high and there is a demand, multiple model centers will be established by clustering the villages based on NDD distribution.

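### Testing banded caregiver burden against prior diagnosis by chi-square discards information that the uncut score would keep; a secondary analysis with a free improvement

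*Protocol article*

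**What the plan says.** The Statistical analysis section of the protocol article gives the chi-square test to pairs of categorical variables, with this example: "such as caregiver burden severity and prior diagnosis of neurodevelopmental disorders (NDD"). The prior-diagnosis variable comes from the Procedures section: "Information on children previously diagnosed with NDD and their history of treatment/rehabilitation will be gathered retrospectively".

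The Caregiver Burden Scale section describes the instrument: "It comprises 15 items rated on a 5-point Likert scale", with items scored from 1 to 5. It says of direction: "The higher the burden, lesser the quality of life". It names no severity categories and no cut-offs.

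Elsewhere in Statistical analysis the same score is left uncut. The t-test is "Applied to compare means between two groups, such as pre- and post-intervention caregiver burden scores", and the ANOVA is "Used to compare differences in continuous outcomes, such as caregiver burden scores and child developmental outcomes, across multiple groups". The logistic regression on a yes/no reduction in burden is a separate analysis and is not at issue here.

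**The concern.** Burden by prior diagnosis compares a many-valued score between two groups, which is the kind of comparison the section gives to the t-test. Sending it to a chi-square means cutting the score into bands first.

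- All differences within a band are lost.
- With three or more bands, the Pearson chi-square also ignores that they run from low to high burden.
- The result can depend on where the cuts fall.

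What is at stake is a lower chance of detecting a real difference between caregivers of previously diagnosed and newly identified children. A chi-square also gives no direct estimate of how large that difference is on the scale.

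**Working it through.** **Inputs from the article.** 15 items, each scored 1 to 5. If items are summed (assumed; the article gives no scoring rule), the total runs from 15 × 1 = 15 to 15 × 5 = 75. The article states no sample size, alpha, power, effect size, SD, share with a prior diagnosis or number of bands. There is therefore no figure of the plan's own to reproduce.

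**Assumptions.** Two-sided alpha 0.05; normal scores with equal SD; uncorrected Pearson chi-square; group sizes 20 against 40 or 64 against 64; bands of equal size unless stated; true difference d in SD units.

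**Formulas (large-sample).**
- Score test: noncentral t with noncentrality d × √(n1·n2/(n1+n2)).
- Chi-square with k bands: noncentral chi-square on k − 1 degrees of freedom, λ = [n1·n2/(n1+n2)] × Σ (p1j − p2j)² / p̄j, where p1j and p2j are the two groups' shares in band j and p̄j is the pooled share.

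**One case by hand: 64 against 64, d = 0.5, two bands cut at the median.**
- Score test: noncentrality 0.5 × √32 = 2.83; power about 80%.
- Shares above the cut: Φ(0.25) = 0.599 and 0.401, a difference of 0.197. λ = 32 × 2 × 0.197²/0.5 ≈ 5.0. On 1 degree of freedom, power is about 61%.
- Relative loss: 1 − 0.61/0.80 = 24%.

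**Simulated power** (6,000 data sets per setting for 20 against 40; a separate simulation for 64 against 64), with relative loss in brackets as 1 − chi-square power / score power:

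| Groups, d | Score t-test | 2 bands | 3 bands | 4 bands |
|---|---|---|---|---|
| 20 vs 40, 0.6 | 58% | 43% (26%) | 39% (33%) | 29% (50%) |
| 20 vs 40, 0.8 | 82% | 65% (21%) | 63% (23%) | 52% (37%) |
| 64 vs 64, 0.5 | 80% | 61% (24%) | 62% (23%) | 56% (30%) |

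With 20 against 40, the four-band chi-square rejects a true null only 3.4% of the time. Part of its loss there is small-sample conservatism.

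**Sensitivity (large-sample formulas).**
- Uneven bands, 64 against 64, score power 80%: a 90/10 split gives 36.5% power (54% loss); 60/30/10 gives 53.9% (33% loss).
- Score power 95%, three to five bands: loss 11% to 27%.
- Over all splits, bandings and power levels tried: loss 11% to 59%.

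**Part due to ignoring order.** With 64 against 64, score power 80% and four equal bands, the chi-square has 56.3% power and a linear trend test on the same bands 72.8%. Order accounts for 72.8 − 56.3 = 16.5 of the 80 − 56.3 = 23.7 points lost. With two bands there is no order to lose, and the two tests coincide.

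**The case against.** The strongest reply is that this is an illustration within a list of methods. Neither primary objective asks whether burden differs by prior diagnosis, and for the centre's effect on burden the plan compares uncut scores. That stands, and it limits the weight of the point.

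Several stronger readings are tempting but not supported:

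- *The chi-square is wrong.* It is a valid test of two categorical variables; it is only less informative here.
- *The plan loses a fixed share of its power, such as a third.* A third lies within the range above, but the loss depends on band number and placement, group split and effect size, none of which the article gives.
- *The bands are undefined.* They are not given in this article. They may be in the full protocol, the analysis plan or the scale's cited source, none of which is shown. With established cut-offs, the worry about where the cuts fall would weaken.
- *The number of affected children is small.* The article gives no count. Its background prevalence figures run from 2% to one in eight, and more than one centre is foreseen if prevalence is high.
- *Banding brings no gain.* Bands can help description and interpretation. Normal scores also favour the t-test, although a rank test kept almost all of its power in the simulations.

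What remains is that the article names a specific method for a specific comparison when a better one is available from data already collected. That is a choice of method, not a detail left to another document.

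**Conclusion.** The point holds as a minor improvement to a secondary analysis. Under the stated assumptions (20 against 40 or 64 against 64, normal scores, two to four equal-sized bands, score-test power of about 58% to 82%), the chi-square gives up roughly 20% to 50% of the power of the score comparison. The direction was the same in every setting tried; the size cannot be fixed from the article. A reader might infer that the trial's main conclusion on caregiver burden is at risk. It is not: the pre-post comparison uses scores and does not depend on this test.

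**What to change.** Replace the chi-square example with one sentence: the Caregiver Burden Scale total will be compared between previously diagnosed and newly identified children by t-test or linear regression (a rank test if clearly non-normal), reporting the mean difference with a 95% interval. Use severity bands for description only, and keep the chi-square for variables that are categorical by nature.

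If a banded comparison is still wanted alongside, a trend or ordinal test would keep the order when there are three or more bands.

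Cost: one sentence in the analysis section, with no new data or visits.

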**Methods:**

The study will commence with screening all preschool children registered in Anganwadi in the designated villages. Tailored model clinics will be set up in these villages based on the prevalence of NDD. Once established, children diagnosed with NDD will undergo rehabilitation for a year. Baseline and endline assessments will be conducted to evaluate the effectiveness of the model center on both the child's disability and the caregiver burden.

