## Materials and methods

### Participants

A single arm study will be conducted among children aged 3 to 5 years attending Anganwadi centers in SRM UBA adopted villages who will be screened for neurodevelopmental disorders with parental consent. Those identified with NDD or previously diagnosed with any form of NDD will be included in the study.

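### The ANOVA of burden and developmental scores across clinics or regions has no baseline term and no allowance for village, although places are not randomised

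*Protocol article*

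**What the plan says.** All references are to the protocol article.

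- **Statistical analysis**, under inferential statistics: ANOVA is to compare "differences in continuous outcomes, such as caregiver burden scores and child developmental outcomes, across multiple groups (e.g., different clinics or geographic regions"). No covariate, change score or random effect is named for this test. Two neighbouring analyses do use such information: the t-test takes pre- and post-intervention burden, and the logistic regression of burden reduction (yes/no) adjusts for confounders such as socioeconomic status and NDD severity.
- **Participants**: "A single arm study will be conducted among children aged 3 to 5 years attending Anganwadi centers". There is no randomised comparison of places.
- **Procedures**: screening is "on all Anganwadi children aged between 3 to 5 years in 12 SRM UBA adopted villages", and "model centers will be established in villages with high prevalence rates". If several centres open, villages are to be grouped by how NDD is distributed. However, "While the initial plan is to set up one model center".
- **Abstract, Methods**: "Baseline and endline assessments will be conducted to evaluate the effectiveness of the model center". Table 1 places caregiver burden and the effectiveness assessment at both t0 and t5.

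**The concern.** Two features of the design do not fit an unadjusted ANOVA on individual children.

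First, where a centre opens, and which villages it serves, depends on NDD prevalence. Families at different clinics or in different regions may therefore differ in burden and severity at entry. An ANOVA without the baseline score cannot separate that difference from a difference in what happened during the year, although each enrolled child and caregiver has a t0 value.

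Second, children are nested in villages, and villages in clinics or regions. If outcomes in the same village resemble each other, an ANOVA that counts every child as independent understates the standard error between groups.

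Table 1 and the Discussion say that findings go to authorities and are meant to guide services elsewhere. A difference between places that only reflects starting levels or village effects could be read as one centre working better than another.

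**Working it through.** The article states no sample size, SD, ICC, children per village or baseline-endline correlation. There is no plan figure to reproduce, and every input below other than the 12 villages is an assumption shown as a range.

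**1. Baseline gap, if endline scores are compared**

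Assume equal SDs at both times, the same baseline-endline correlation r in every clinic, and no clinic effect. Let d be the baseline gap in SD units.

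Spurious endline gap = r × d. For d = 0.5:
- r = 0.3: 0.3 × 0.5 = 0.15 SD
- r = 0.5: 0.5 × 0.5 = 0.25 SD
- r = 0.7: 0.7 × 0.5 = 0.35 SD

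A simulation (10,000 runs, 3 clinics of 40 children, one clinic 0.5 SD higher at baseline, no clinic effect, nominal level 5%) gave rejection by the endline-only ANOVA in 10%, 19% and 33% of runs for r = 0.3, 0.5 and 0.7.

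Under the same model, change scores leave a gap of −(1 − r) × d: −0.35, −0.25 and −0.15 SD. ANCOVA on the baseline score leaves about zero.

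**2. Precision gained from the baseline score**

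Residual variance under ANCOVA = 1 − r².
- r = 0.3: 1 − 0.09 = 0.91, a cut of 9%
- r = 0.5: 1 − 0.25 = 0.75, a cut of 25%
- r = 0.7: 1 − 0.49 = 0.51, a cut of 49%

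**3. Village clustering**

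Only enrolled children with NDD contribute endline scores, so the cluster size m is enrolled children per village, not children screened. Assume m = 5, 10 or 20. At the Background's one in eight, these need 5 × 8 = 40 to 20 × 8 = 160 preschoolers per village.

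Design effect = 1 + (m − 1) × ICC. Ratio of true to naive SE = √(design effect).

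Type I error was simulated with 20,000 runs, 12 villages in 3 clinics of 4, no true clinic difference and nominal level 0.05:

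| m | ICC | Design effect | SE ratio | Type I error, ANOVA on children |
|---|---|---|---|---|
| 5 | 0.01 | 1.04 | 1.02 | 0.059 |
| 5 | 0.05 | 1.20 | 1.10 | 0.081 |
| 5 | 0.10 | 1.40 | 1.18 | 0.119 |
| 10 | 0.01 | 1.09 | 1.04 | 0.065 |
| 10 | 0.05 | 1.45 | 1.20 | 0.128 |
| 10 | 0.10 | 1.90 | 1.38 | 0.207 |
| 20 | 0.01 | 1.19 | 1.09 | 0.082 |
| 20 | 0.05 | 1.95 | 1.40 | 0.218 |
| 20 | 0.10 | 2.90 | 1.70 | 0.362 |

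With 2 clinics of 6 villages the range over the same m and ICC is 0.055 to 0.249. With ICC = 0 the ANOVA on children is correct (0.048 to 0.052). ANOVA on village means holds 0.048 to 0.053 in every scenario.

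**The case against.** The strongest reply is that this is a supporting analysis introduced with examples. The primary objectives are prevalence and impact on caregiver burden, and impact is addressed by the pre-post t-test and the adjusted logistic regression. Covariates and random effects for a secondary comparison are often left to a fuller document. With one centre planned at first, a clinic contrast may never arise.

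Much of this stands and limits the weight of the point. It does not remove it: the article names a specific inferential method for a specific contrast, and that method suits non-randomised, nested places poorly. A regional comparison remains possible with a single centre.

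Several stronger readings are tempting but not supported:

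- **That raw endline scores are certainly what is compared.** The text does not say endline or change. Change scores would alter the baseline problem but not the clustering one.
- **That the intervals are too narrow in any case.** This needs ICC > 0 and several villages per compared group. If the groups are the villages themselves, village is the tested factor and the clustering point falls away. At small ICC and few children the inflation is slight.
- **That the design effect can be worked out from all screened children.** Endline scores exist only for enrolled cases. At the 2% disability figure in the Background, even 5 cases per village would need 5 / 0.02 = 250 preschoolers, so clusters could be smaller than assumed here.
- **That a clinic starting with higher burden must look worse at endline.** The carried-over gap is r × d, and a larger improvement outweighs it.
- **That these contrasts feed the dashboards, or that siblings sharing a caregiver add clustering.** The article lists utilisation, burden trends and regional prevalence for the dashboards, and does not mention siblings.

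**Conclusion.** The point holds in a limited form. As published, the comparison of scores across clinics or regions is an ANOVA with neither baseline adjustment nor allowance for village, in a design where places are selected or grouped by NDD prevalence and baseline scores are available.

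If endline scores are used, a 0.5 SD baseline gap produces a spurious 0.15 to 0.35 SD endline gap (r 0.3 to 0.7). If several villages fall within a compared group, the true SE is 1.02 to 1.70 times the naive one (5 to 20 enrolled children per village, ICC 0.01 to 0.10). All these inputs are assumed, so the figures show plausible sizes, not expected ones.

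This is a secondary analysis. The pre-post burden comparison does not depend on it. The change is worth making because it is nearly free, not because the main conclusion is at risk.

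**What to change.** Reword the ANOVA paragraph of the Statistical analysis section along these lines:

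- Compare places by ANCOVA: endline score on baseline score, NDD severity and group. State explicitly that the outcome is the endline score.
- Where villages are nested within the compared groups, add village as a random effect or analyse village means. Where the groups are the villages, leave the random effect out, because it could not be separated from the group effect.
- Compare clinics only if more than one centre opens.
- Report every comparison between places as descriptive, with intervals. Adjustment removes only confounding through what was measured.

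**Cost.** This changes wording only. No extra data are needed, and SPSS, the named software, fits both models. Allowing for village widens the between-place intervals. Twelve villages carry limited information: comparing village means leaves 12 − 3 = 9 degrees of freedom with three groups and 12 − 2 = 10 with two. ANCOVA and change-score analyses can give different answers when groups differ at baseline, so the choice should be fixed before endline data are seen.

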The model center, or specialist outreach center, is envisioned to have trained physiotherapists for children's rehabilitation, with pediatric physicians visiting the centers for progress checks and further evaluations. Equipped with essential tools such as swiss ball, peanut ball, obstacle for gait training, balance boards,etc., the center will provide pediatric rehabilitation and group therapies for children. Discussions and arrangements will be initiated with village authorities to position the model center close to or within school/Anganwadi premises.

Subsequent to NDD identification in children, baseline assessments of NDD will be conducted alongside qualitative assessment of caregivers' perspectives and experiences regarding accessing rehabilitation services in the community. Quantitatively, caregiver burden will be evaluated using a caregiver burden scale.

Upon enrollment, children will undergo physiotherapy rehabilitation for one year under a trained physiotherapist, with routine screenings by pediatricians. The neurodevelopmental rehabilitation will include sensorimotor training, motor learning, sensory integration, motor training and neurodevelopmental therapy which will be tailored according to the individual’s needs and the severity and type of disorder. Treatment will be given in person, in group or as individual therapy. The entire timeline and flow have been illustrated in Table 1.

**Table 1 Tab1:** Spirit timeline for the study

	Enrolment and allocation		Post allocation				Endline evaluation	Close-out
Time point	− t1	t0	t1	t2	t3	t4	t5	t7
Preliminary screenings	X							
Parental consent	X							
Analysis of prevalence	X							
Eligibility screen		X						
Obtained signed parental consent		X						
Allocation		X						
Baseline assessments		X						
Establish model centre		X						
One year rehabilitation			X	X	X	X		
Routine follow up screenings by pediatricians			X	X	X	X		
Baseline tools	X	X					X	
Effectiveness of intervention		X					X	
Caregiver burden		X					X	
Data entry and analysis	X						X	
Share findings with authorities	X							X
Final reports								X
Plan future studies								x

Each t indicates 3 months of time span

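### The planned logistic regression cannot estimate the intervention's impact on caregiver burden, because every participant in this single-arm study receives the intervention

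*Protocol article*

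**What the plan says.** All references are to the protocol article.

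- **Design (Participants).** "A single arm study will be conducted among children aged 3 to 5 years attending Anganwadi centers in SRM UBA adopted villages". On entry: "Those identified with NDD or previously diagnosed with any form of NDD will be included in the study". No untreated or comparison group is described in any section. The allocation row in Table 1 has no second group attached to it.
- **Exposure (Procedures).** "Upon enrollment, children will undergo physiotherapy rehabilitation for one year under a trained physiotherapist".
- **Outcome timing (abstract, Methods).** "Baseline and endline assessments will be conducted to evaluate the effectiveness of the model center on both the child's disability and the caregiver burden". Table 1 places caregiver burden at t0 and t5 only.
- **Logistic model (Statistical analysis).** Its purpose is given as follows: "Binary Logistic Regression: This will help us identify the impact of the intervention on the binary outcome (reduction in caregiver burden, yes/no"). The adjustment is worded as "controlling for potential confounding variables (e.g., socioeconomic status, severity of NDD").
- **Separate pre/post comparison (same section).** A t-test is "Applied to compare means between two groups, such as pre- and post-intervention caregiver burden scores".

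**The concern.** The stated purpose of the logistic model is to measure what the intervention does. That needs families with and without the intervention, or at least an outcome observed under both conditions. The design supplies neither for this model. The adjustment for confounders has the same difficulty: a confounder distorts a comparison between exposed and unexposed, and here there is no such comparison.

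Caregiver burden is the primary outcome measure, and the centre's impact on it is a primary objective. The logistic model is the only covariate-adjusted analysis that the article names. If it is run as described, software will drop the intervention term or fail to estimate it. What remains is a set of odds ratios for socioeconomic status and severity, plus an overall proportion improved. Either could be reported as the impact of the centre. The Discussion intends the results to serve as a model for centres elsewhere in Tamil Nadu and to guide government strategy, so such a misreading would carry weight.

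**Working it through.** The article gives no figure for this analysis, so there is nothing to reproduce. The question is whether the intervention coefficient is identifiable.

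**Step 1. Write the model.** For caregiver i, let Y = 1 if burden fell and 0 otherwise, and let T = 1 if the family received the intervention. With the two example covariates:

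logit P(Y = 1) = b0 + b1·T + b2·SES + b3·severity

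**Step 2. Put in the design.** Participants (single arm) and Procedures (rehabilitation on enrolment) give T = 1 for everyone, so

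logit P(Y = 1) = (b0 + b1) + b2·SES + b3·severity

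Only the sum b0 + b1 enters the likelihood. Any value of b1 fits equally well if b0 moves to compensate.

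**Step 3. Check numerically.** Data were simulated for an assumed 100 families. The size and the data are illustrative only and do not affect the conclusion.

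- Design matrix [intercept, T, SES, severity]: 4 columns, rank 3.
- Log-likelihood with b1 fixed and b0 shifted by the opposite amount:

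| b1 | log-likelihood |
|---|---|
| -5 | -56.686 |
| -1 | -56.686 |
| 0 | -56.686 |
| 1 | -56.686 |
| 5 | -56.686 |

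The likelihood is flat in b1. Neither more families nor more covariates would change this.

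**Step 4. Can time stand in for the exposure?** No. A yes/no reduction is already a change from baseline. It takes one value per caregiver and is undefined before treatment, so there is no pre-treatment Y to set against a post-treatment Y.

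**Step 5. What can the model estimate?** b2 and b3 are estimable. They are associations of socioeconomic status and severity with the odds of improvement among treated families. The combined intercept reflects the proportion who improved at reference covariate values. None of these is an effect of the intervention.

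**The case against.** **Exposure may vary among treated families.** The article never says how the intervention enters the model. Dose, intensity and number of sessions are adapted to functional goals, therapy may be individual or in groups, there may be more than one centre, and clinic utilisation is to be tracked. Coding of a term is a detail that an article may leave to an analysis plan. This is fair as far as it goes: a model with a dose term could be fitted, and adjustment would then have a purpose. It does not rescue the stated aim. None of these quantities is named as a model term. A dose set by each child's goals is confounded by the reasons for setting it, and attendance is chosen by the families. All such contrasts compare treated with treated.

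**The primary outcome does not depend on this model.** This stands. A reader might infer that the trial has no usable analysis of caregiver burden. The documents do not support that, because the t-test addresses the continuous score before and after. The flaw is confined to what the logistic model is said to deliver.

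**Dichotomising the score.** A reader might also infer that the yes/no outcome will make the programme look successful through measurement noise alone. The documents do not support that either. The article does not define a reduction, so it cannot be assumed that any small drop counts. It gives no standard deviation for the scale, and the only reliability figure is Cronbach's alpha, which measures internal consistency and not stability over a year. No misclassification rate can be derived from this.

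**Conclusion.** The analysis is wrong as written. In a single-arm study where all enrolled children are to be treated, the logistic regression cannot estimate the impact of the intervention. The loss is complete for that purpose: the coefficient has no estimate and no confidence interval at any sample size. It does not extend to the before-after change in burden score, which can be estimated.

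This is a purpose the article states and its own design cannot meet. It is not a detail left to a fuller document.

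The conclusion rests on two readings of the text: that there is no comparison group, and that the outcome is one change status per caregiver. Both follow from the article's wording. It needs no assumption about sample size, variability or the threshold for a reduction.

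Correcting the model does not create a controlled comparison. The paired change will still combine any effect of the centre with time, the children's maturation and regression to the mean.

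**What to change.** In the Statistical analysis section:

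1. Delete the statement that the logistic regression shows the intervention's impact. Describe it as a model of predictors of improvement among treated families, and describe its covariates as predictors, not confounders.
2. Add baseline burden to that model, since a caregiver's starting score affects both the room to improve and regression to the mean.
3. Build on the t-test already planned. State that it is paired within caregiver, and report the mean change in the continuous Caregiver Burden Scale score (endline minus baseline) with a 95% confidence interval as the main pre/post estimate.
4. Describe that estimate as an uncontrolled before-after change that cannot separate the intervention from time, maturation or regression to the mean.

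The cost is rewording and minor analysis work. No new data are needed, because the baseline and endline scores are already to be collected. The change is best made before the endline data are analysed.
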